## Introduction

### Risk-Stratified Management of Chronic Disease Patients

Chronic diseases affect approximately 52% of Americans and consume 86% of health care costs [1]. Example management strategies for care include case management, disease management, supported self-care, and wellness promotion (listed in Table 1 in descending order of intensity). Each strategy is widely used and has its own benefits and properties [2,3]; for example, most major employers purchase and nearly all private health plans offer case management services [2,4] targeting early interventions at high-risk patients to prevent large expenditures and avoid deterioration of health status. Proper use of case management can reduce hospital admissions and readmissions and emergency department visits by up to 30% to 40% [3,5-9], lower costs by up to 15% [6-10], and improve patient satisfaction, quality of life, and treatment adherence by 30% to 60% [5]. A case management program can cost more than US $5000 per patient per year [6] and typically enrolls only 1% to 3% of targeted patients due to resource limitations [11]. For maximal benefit, only patients expected to incur the highest costs and/or those with the poorest prognoses should be enrolled.

**Table 1 table1:** Description of patient management strategies.

Management strategy	Description
Case management	“A collaborative process that assesses, plans, implements, coordinates, monitors, and evaluates the options and services required to meet [a patient’s] health and human service needs” [12]. It involves a case manager who calls the patient periodically, helps make doctor appointments, and arranges for health and health-related services.
Disease management	Example intervention: check electronic medical records to find and call high-risk patients with the disease who require a specific test, but have not had it for ≥2 years.
Supported self-care	Example intervention: give patients electronic monitoring tools for self-management.
Wellness promotion	Example intervention: mail educational materials on how to maintain health.

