Using Intermountain Healthcare data, we will demonstrate our techniques on the test case of asthma patients. In the United States, asthma affects 18.7 million adults (8%) [53] and 7.1 million children (9.6%) [54,55]. Patient management strategies such as case management can ensure proper care to reduce asthma exacerbations, improve school attendance and performance, and reduce hospitalizations and emergency department visits. This impacts both quality of life and 63% of total annual asthma costs attributable to asthma exacerbations [8,56].

Our analysis results will use different combinations of attributes to determine the minimum performance requirement and allow tradeoffs for adapting use of our models beyond our setting based on available attributes. Our results will provide a cornerstone to expand testing of our techniques on other clinical datasets, patient populations, and diseases beyond asthma in the future. As patient status and feature patterns associated with high risk change over time, our techniques can be periodically reapplied (eg, to move patients across different management levels and identify newly occurring feature patterns).

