As mentioned previously, identifying asthma requires medication order and refill information. Our dataset includes this information because Intermountain Healthcare has its own health insurance plan (SelectHealth [78]). If the Intermountain Healthcare EDW is missing too much refill information, we will use claim data in the all-payer claims database [76] to compensate. If adding physician profile features cannot significantly increase prediction accuracy for asthma, we will choose chronic obstructive pulmonary disease or heart diseases for Aims 1 to 4.

We have a large dataset. If we experience scalability issues using Weka, we will use a parallel machine learning toolkit, such as Spark’s MLlib [79-81], to build predictive models on a secure computer cluster available to us at the University of Utah Center for High Performance Computing [82].

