#### Threshold Computation Algorithm

We will conduct quantitative analysis to determine the optimal management level for each risk percentile. We will proceed through the risk percentiles one by one, from the highest to the lowest. Given a risk percentile, we will compute for each management level the average future cost per patient in the percentile if patients in the percentile are put into the level. The level with capacity remaining in its management program and the lowest average future cost per patient will be chosen for the risk percentile.

More specifically, consider a risk percentile and an average patient whose predicted risk falls into the percentile. If the patient is enrolled in a management program, we estimate that the patient’s future cost will change by delta = the program’s cost – the program’s benefit gained by reducing undesirable events=*c*
_
*i*
_–*avg_n*
_
*e*
_**p***c*
_
*e*
_ compared with no enrollment. Here, *c*
_
*i*
_ is the program’s average cost per patient. Factors such as increased medication cost due to better medication adherence are included in *c*
_
*i*
_. *avg_n*
_
*e*
_ is the average number of undesirable events that a patient in the risk percentile will experience in the future. *p* is the percentage of undesirable events the management program can help avoid, reflecting the program’s benefit. *c*
_
*e*
_ is the average cost of experiencing the undesirable event once. *c*
_
*i*
_ and *p* can be obtained from statistics reported in the literature for the management program [39,88]. *avg_n*
_
*e*
_ can be obtained by making predictions on historical data and checking the corresponding statistics for the risk percentile. *c*
_
*e*
_ is obtained from statistics on historical data. The management level with the smallest delta is optimal for the risk percentile. If no statistics on *c*
_
*i*
_ and *p* of a management program are available in the literature, the clinician in our research team ([name]) will provide rough estimates based on experience. We will perform sensitivity analysis when choosing thresholds by varying the estimated values of *c*
_
*i*
_ and *p* to obtain the full spectrum of possible outcomes in Aim 4.

The preceding method performs an exhaustive search among all management levels for each risk percentile. In practice, we would expect *avg_n*
_
*e*

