#### Estimate Outcomes

Given a set of attributes and a predictive model, we will estimate each outcome. We will use the same method as in Aim 1 to train the model on the first 10 years’ data. For the 11th year’s data, we will obtain prediction results, compute thresholds for risk strata, then estimate the outcome in a way similar to Aim 3. For example, consider a patient who will have a cost of *h* and experience *n*
_
*e*
_ undesirable events in the following year with no program enrollment. If the patient is enrolled in a management program, we estimate that the patient’s future cost will become *h* + *c*
_
*i*
_–*n*
_
*e*
_**p***c*
_
*e*
_, where *c*
_
*i*
_, *p*, and *c*
_
*e*
_ are as defined in Aim 3. The overall outcome estimate is the aggregate of estimated outcomes for all patients. Using a similar approach, we can identify the minimum accuracy requirement of the model for it to be clinically valuable.

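### Aims 3 and 4 treat observed events and costs as if no patient had been in a management program; for any patient already managed, the program effect is counted twice

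*Protocol article*

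**What the plan says.** **The target quantity is the unmanaged state.** Under Aim 3 (Threshold Computation Algorithm), the change in a patient's future cost is delta = c_i − `avg_n_e` × p × c_e, "compared with no enrollment". Here p "is the percentage of undesirable events the management program can help avoid, reflecting the program’s benefit". Under Aim 4 (Estimate Outcomes), h and n_e are the patient's cost and "undesirable events in the following year with no program enrollment", and enrollment turns h into h + c_i − n_e × p × c_e.

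**The source is observed records.** In Aim 3, `avg_n_e` "can be obtained by making predictions on historical data and checking the corresponding statistics for the risk percentile". In Aim 4: "For the 11th year’s data, we will obtain prediction results, compute thresholds for risk strata, then estimate the outcome". No other source for h or n_e is named.

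**The setting is one where programs already exist.** The Introduction says that "most major employers purchase and nearly all private health plans offer case management services", and that risk stratification is in wide use, with asthma named. The section on problems with the current approach reports health plans in 9 of 12 communities using predictive models to find case-management candidates. The Discussion says such models are already in common use for case management. Aim 1b (Sample Size Justification) notes that "Intermountain Healthcare has its own health insurance plan".

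**Prior enrollment is not mentioned.** It is absent from the Patient Attributes list, which is described as partial. Nothing says that enrolled patient-years are identified, excluded or adjusted. The planned sensitivity analyses vary c_i, p, the attribute set and the uptake of suggested interventions, but not prior enrollment.

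**The concern.** Observed records equal the no-enrollment state only if nobody in them was enrolled. Where some patients were, three things go wrong for those patients:

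- The event count fed into the formula has already been lowered by a program, and p lowers it again.
- The observed cost h may already contain the program's cost, and c_i adds it again.
- The training label reflects risk under management, so the model learns a lower risk than the patient would have unmanaged.

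Programs aim at the highest-risk patients, so the bias would tend to sit in the upper percentiles, where the case-management threshold is set. Because Aim 3 chooses a level percentile by percentile, a local bias can move a threshold even if the population average hardly changes. The absolute outcome estimates feed the minimum accuracy requirement (Estimate Outcomes) and the table to be published for other health systems (Sensitivity Analysis).

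**Working it through.** **Plan's own figure.** The only sample size tied to the Aim 4 primary outcome is 857 (paired log cost, 0.1 SD, one-sided .05, 90% power). It reproduces: ((1.645 + 1.282)/0.1)² rounds up to 857. The point below does not depend on it.

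**Inputs.** p = 0.30 to 0.40, from the Introduction's figure of up to 30% to 40% fewer admissions and emergency visits under case management. The share m of a risk percentile already managed is not in the documents and is shown as a range. Unmanaged events per patient are set to 1. Two assumptions are added: past programs had the same p, and managed and unmanaged patients in a percentile have the same unmanaged event rate.

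**One patient already managed.**
- Observed events: 1 − p = 0.70 or 0.60.
- Events after simulated enrollment: (1 − p)² = 0.49 or 0.36. Counting the effect once gives 0.70 or 0.60.
- Further benefit credited: (1 − p) × p = 0.21 or 0.24. The true additional benefit of a program the patient already has is 0.
- Cost: if the recorded cost includes the program, observed h = h₀ + c_i − p × c_e, where h₀ is the unmanaged cost. The plan's formula then gives h₀ + 2c_i − [1 − (1 − p)²] × c_e, so the program is paid for twice and 0.51 or 0.64 of unmanaged events are credited as avoided instead of 0.30 or 0.40.

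**A percentile with share m already managed.**
- Observed `avg_n_e` = 1 − m × p.
- Benefit in the plan = (1 − m × p) × p.
- Benefit against no enrollment = p, so the plan understates it by the fraction m × p.
- Gain over the status quo = (1 − m) × p, so the plan overstates it by the factor (1 − m × p)/(1 − m).

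| m (assumed) | Understatement against no enrollment, p = 0.30 / 0.40 | Overstatement factor against status quo, p = 0.30 / 0.40 |
|---|---|---|
| 0 | 0 / 0 | 1.00 / 1.00 |
| 3% | 0.9% / 1.2% | 1.02 / 1.02 |
| 25% | 7.5% / 10% | 1.23 / 1.20 |
| 50% | 15% / 20% | 1.70 / 1.60 |

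**Effect on a threshold (illustration).** A program pays for itself when `avg_n_e` × c_e reaches c_i/p. Taking c_i = US $5000 (the Introduction says case management can cost more than this), the break-even is 5000/0.30 = $16,667 or 5000/0.40 = $12,500 of event cost per patient. With m = 50%, the unmanaged event cost must reach 16,667/0.85 = $19,608 or 12,500/0.80 = $15,625 before the observed data show break-even.

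**Does varying p cover this?** Only in part. Within one percentile, scaling `avg_n_e` by 1 − m × p is the same as lowering p to p × (1 − m × p). But p is defined per program, while m would differ by percentile, and no choice of p repairs the training labels or the ranking.

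**The case against.** **The premise is not documented for this system.** Nothing says that its asthma patients were in a program. The statements on case management are general background, and the health plan is mentioned only to explain why refill data exist. This stands as a limit on size: the error may be zero. It does not remove the point, because the article's own account makes zero enrollment doubtful and the plan does not state it as an assumption.

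**A condensed article may leave this detail to a fuller document.** The article names the right target quantity, and the attribute list is partial. But it also fixes the formulas and their data source, and that source does not by itself deliver the stated quantity.

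**The two-model comparison is protected.** Both models are applied to the same patients with the same h, n_e, p and c_i, so much of the bias cancels in the primary test. This largely stands. Cancellation is incomplete: a managed patient whom one model ranks below the cut keeps the program-reduced count with no new enrollment. Physician features such as mean outcome and mean cost also reflect existing management. The direction is unknown.

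**Stronger readings that the documents do not support.**
- A reader might infer that simulated benefit is 30% to 40% too small throughout. That holds only at m = 1 and only against no enrollment; against the status quo the error runs the other way.
- A reader might apply the Introduction's 1% to 3% enrollment to all asthma patients (270 to 810 of 27,000 children, 750 to 2,250 of 75,000 adults) and conclude that managed patients fill the top percentiles. The 1% to 3% refers to targeted patients in general, not to this system. Filling the top percentiles would also need near-perfect targeting, whereas the article reports that more than 80% of the costliest 1% are missed by the top 1% risk group.
- A reader might see a direct safety problem, because the article foresees reapplying the techniques to move patients between levels. This study is a simulation on deidentified records and moves no patient, clinicians keep the final decision, and implementation is left to future work. The point matters for later reuse only.

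**Conclusion.** The concern holds as an unstated and doubtful assumption in Aims 3 and 4. Quantities defined without a program are taken from records of care that may have included one. For each patient already managed, the effect is counted twice (0.49 to 0.36 of unmanaged events instead of 0.70 to 0.60), and program cost may be counted twice too.

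At percentile level the size depends on m, which the documents do not give: nothing at m = 0, about 1% at m = 3%, and 15% to 20% at m = 50%, as understatement against no enrollment. These figures rest on p at the upper values quoted in the Introduction, on past and simulated programs having the same p, and on equal unmanaged risk within a percentile.

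Thresholds and published absolute estimates are most exposed; the comparison of models with and without physician features is only partly exposed. The point is a should-fix. A must-fix would need evidence of substantial prior enrollment in the upper percentiles, which the documents do not contain.

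**What to change.** - **Where enrollment is recorded** in the data warehouse or the system's health plan: flag those patient-years. Exclude them from, or adjust them in, model training and the estimation of `avg_n_e`, n_e and h, as a primary or a sensitivity analysis. An adjustment should restore the unmanaged event count and remove program cost from h.
- **Where it is not recorded:** state that observed data are treated as unmanaged, and add a sensitivity analysis over m, by risk percentile, to the planned variation of c_i and p.
- **In either case:** state that predicted risk means risk under the care observed unless corrected, and say whether reported benefit is against no enrollment or against the status quo.

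**Cost.** If the records exist, an addition to the data extract and to the simulation; if not, one stated assumption and one more varied parameter. Exclusion loses some high-risk patient-years. Adjustment depends on p, and dividing a count by 1 − p leaves a patient with zero observed events at zero, so it works on averages rather than individuals. Programs run by other payers or employers may not be visible, so the sensitivity analysis over m remains useful even when the system's own enrollment is known.

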#### Sensitivity Analysis

Intermountain Healthcare collects an extensive set of attributes. Another health care system may collect only a subset of these attributes. To ensure the model’s generalizability, we will test various combinations of attributes and estimate outcomes when the modified model is used. The estimate will identify which attributes are critical. If an important attribute is unavailable in a specific health care system, the estimate can suggest alternative attributes with minimal negative impact on outcomes.

Our full model will use up to 400 attributes. It is not possible to conduct simulations for every possible combination of these attributes. Instead, we will use an attribute grouping approach associating attributes likely to coexist, such as attributes associated in a laboratory test panel, based on our clinical expert’s judgment. We will construct and publish a table listing possible combinations of attributes by groups, including outcomes estimated through simulations and the predictive model’s trained parameters. A health care system interested in deploying the model can use the table to determine expected outcomes for their data environment and identify attributes that need to be collected. One entry in the table will correspond to the attributes available in the Observational Medical Outcomes Partnership (OMOP) common data model [89], which standardizes clinical and administrative attributes from more than 10 large health care systems in the United States [90]. The model in this entry will directly apply to at least those health care systems. If conducting simulations for the many combinations of attribute groups is too slow on one computer, we will parallelize simulations on a secure computer cluster available to us [82].

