### Datasets and Test Cases

This study will use a large clinical and administrative dataset in Intermountain Healthcare’s enterprise data warehouse (EDW) for all 4 aims. Intermountain Healthcare is the largest health care system in Utah, with 185 clinics and 22 hospitals. Intermountain Healthcare’s EDW contains approximately 9000 tables and an extensive set of attributes [51]. Partial lists of patient and physician attributes follow.

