###### Accuracy Evaluation and Sample Size Justification

We have 11 years’ data. We will use a standard approach to train and test predictive models. We will conduct stratified 10-fold cross validation [74] on the first 10 years’ data to train and estimate the accuracy of models. The 11th year’s data will be used to assess the best models’ performance reflecting use in practice. For categorical outcome variables, we will use the standard performance metric of the area under the curve (AUC) of the ROC [74] to select the best model. For continuous outcome variables, we will use the standard performance metric of *R*
^
*2*
^ to select the best model and also report the Cumming’s prediction measure (equivalent to the mean absolute prediction error) [25,32]. To determine the clinical, administrative, and environmental variable attributes essential for high accuracy, backward elimination [48] will be used to drop independent variables as long as the accuracy does not drop by more than 0.02.

We will test the hypothesis that adding physician profile features can increase prediction accuracy twice—once for children and once for adults. We will compare the accuracies achieved by 2 predictive models using the best machine learning algorithm. The first model will use patient, physician profile, and environmental variable features; the second, only patient and environmental variable features. We will accept the hypothesis if the first model achieves higher accuracy (AUC or *R*
^
*2*
^) than the second model by 10% or more.

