## Discussion

Our techniques’ principles are general and rely on no special property of any disease, patient population, or health care system. Just as predictive models are used for case management for various diseases and patient populations [13,24,30,31], after proper extension our techniques can be used for a range of decision support applications in various settings (see the innovation subsection of the Introduction). Our simulation method will determine how to generalize a predictive model to differing sites collecting different sets of attributes and the attributes most important for generalization. Using data from an integrated health care system with many heterogeneous facilities spread over a large geographic area, we will demonstrate our techniques on the test case of asthma patients. These facilities include 22 hospitals and 185 clinics, ranging from tertiary care hospitals in metropolitan areas staffed by subspecialists to community urban and rural clinics staffed by family physicians and general practitioners with limited resources. Variation in geographic location, patient population, cultural background, staff composition, and scope of services provides a realistic situation to identify factors generalizable to other facilities nationwide. When conducting simulations for each disease (pediatric/adult asthma), one of the models produced will directly apply to 10 or more large health care systems.

Because inaccurate predictive models are commonly used already for case management [24], we would expect our more precise models to have practical value. Future studies will demonstrate our techniques on other diseases, test cases, and patient populations, implement our techniques in a major health care system for risk-stratified management of asthmatic children, and test the impact in a randomized controlled trial.

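### No planned test holds out physicians, clinics, regions or systems, so the statements that a model will apply directly to 10 or more other health systems, and that its outcome table can be read there, are untested

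*Protocol article*

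**What the plan says.** All references are to the protocol article.

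- **Data.** One organisation's data serve the whole study: "enterprise data warehouse (EDW) for all 4 aims" (Datasets and Test Cases).
- **Validation.** "We will conduct stratified 10-fold cross validation [74] on the first 10 years’ data to train and estimate the accuracy of models". Then: "The 11th year’s data will be used to assess the best models’ performance reflecting use in practice" (Aim 1a, Accuracy Evaluation and Sample Size Justification). The article mentions no grouping of folds by physician or facility.
- **Aim 4 split.** The same one: "We will use the same method as in Aim 1 to train the model on the first 10 years’ data", with outcomes estimated on year 11 (Aim 4, Estimate Outcomes).
- **Generalizability analysis.** Attribute groups are removed and outcomes re-estimated. The resulting table is to be published, and another health care system "can use the table to determine expected outcomes for their data environment" (Aim 4, Sensitivity Analysis).
- **Transfer claim.** For the common-data-model entry: "The model in this entry will directly apply to at least those health care systems" (same section). The Discussion repeats it: "one of the models produced will directly apply to 10 or more large health care systems".
- **Features under test.** Physician profile features include the mean outcome and average cost of a physician's own patients, and the physician's age, years in practice and specialty (Physician Profile Features). The index patient is left out of the profile (Framework).

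**The concern.** Moving a model to another system changes at least three things: which attributes exist, who the physicians and clinics are, and what the local event rates and costs are. The plan varies the first, and the passage of time. It does not vary the second or third, yet its conclusion covers all three.

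This matters more than usual because the ingredient being tested is physician profile features. Age, years in practice, specialty, panel counts, mean outcome and mean cost, taken together, may partly act as a label for a physician or clinic. A flexible learner that meets the same physicians in training and in test can then score well by recalling local risk levels, and that part of the gain need not travel. Leaving the index patient out of the profile does not prevent this, because the label remains.

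At stake are the credibility of the physician-feature gain as a transferable result, and a published table that other systems are invited to use for planning.

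**Working it through.** **1. The plan's own figure.** The only related number is the Aim 4 sample size. One-sided α = .05, 90% power and an effect of 0.1 SD give n = ((1.645 + 1.282)/0.1)² ≈ 856.4, rounded up to the stated 857. It reproduces and is not at issue.

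**2. What each planned check varies.**

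| Check | Attributes | Time | Physicians or clinics held out | System |
|---|---|---|---|---|
| 10-fold cross-validation, years 1–10 | no | no | no | no |
| Year-11 test | no | yes | no | no |
| Aim 4 attribute table | yes | yes | no | no |

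**3. Physician overlap under ungrouped folds.** Inputs: about 27,000 children and 75,000 adults with asthma in year 11; more than 400 pediatric and more than 600 adult primary care physicians (Summary Statistics of the Dataset).

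- Average panel: 27,000/400 = 67.5 children; 75,000/600 = 125 adults. These are upper averages, because the physician counts are minimums.
- If a physician has m patients in the data, a test patient has at least one same-physician patient in the training folds with probability 1 − 0.1^(m−1).
- m = 2 gives 90%; m = 5 gives 99.99%; at the average panel it is essentially 100%.
- With strongly skewed panels (assumed lognormal, sigma 1.5) the share still exceeds 99.9% in both groups.

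For year 11 the overlap depends on physician turnover, which the article does not give. Because that split is by calendar time only, every continuing physician and clinic is on both sides.

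**4. Can the optimism be sized?** Simulation with assumed inputs: 400 physicians, 68 patients each per year, logistic model with intercept −2.5 and patient slope 1, patient-only AUC 0.73–0.75, and physician effects with SD 0.3, 0.5 or 0.8 on the logit scale. The fitted model uses the physician's mean outcome as its feature. Change in AUC against the patient-only score:

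| Test setting | SD 0.3 | SD 0.5 | SD 0.8 |
|---|---|---|---|
| Same physicians | +0.007 | +0.026 | +0.061 |
| New site, own 10-year profiles | +0.008 | +0.026 | +0.058 |
| New site, own 1-year profiles | −0.003 | +0.010 | +0.044 |
| Profiles permuted across physicians | −0.008 | −0.022 | −0.052 |

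The planned design reports only the first row. Which later row applies elsewhere depends on how much of the gain is a recomputable feature and how much is recall, and no planned test shows that. The permuted row is a worst case: it gives new physicians someone else's stored effect. The middle rows rest on one feature in a logistic model and do not exclude memorisation by more flexible learners.

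**5. The tabulated outcomes.** The Aim 4 estimate for an enrolled patient is h + c_i − n_e × p × c_e. Here h and n_e are the patient's own cost and events, taken from this system's year 11, and c_e comes from historical data. Only c_i and p are sought in the literature. A site with other event rates or unit costs gets a different answer even if the model ranks its patients equally well.

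**The case against.** The strongest reply has four parts.

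- **Generalization is framed as attribute availability.** The Innovation and Aim 4 sections speak of sites that collect different attributes, and varying attributes answers that question. Testing on other datasets and populations is left to later work. This stands as a reading of intent. It does not cover telling other systems that they can read expected outcomes from the table, or the flat statement that the model applies to them.
- **The features are recomputable.** No physician identifier is listed, and a new site would build profiles from its own records. A reader might infer from the permuted row that the gain will reverse for new physicians. The documents do not support that: the reversal is produced by the permutation, and with ten years of local history the simulated gain carries over almost intact.
- **The inflation is below the decision rule.** The hypothesis needs a 10% gain, powered as 0.1 in AUC. The largest simulated gain is 0.061, also below 0.074 (10% of a 0.74 baseline). By itself it would not produce a positive Aim 1a. This stands, so a reader should not conclude that Aim 1a or Aim 4 would be answered wrongly.
- **Year 11 may include new physicians.** It is tempting to say that every test keeps the same physicians and clinics. The article does not say so. What it supports is that none are held out by design, and that new ones are not reported separately.

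It is also true that leaving out facilities still tests only one system.

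**Conclusion.** The point holds in a limited form. No planned test holds out physicians, clinics, regions or systems, so the direct-application and expected-outcomes statements go beyond what the study will test. Common-data-model attributes support only the claim that the model can be run elsewhere.

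Overlap is nearly complete in ungrouped cross-validation, assuming random allocation to folds. In year 11 it is of unknown but probably large extent. The planned tests therefore cannot separate transferable gain from local memory. How far the physician features act as identifiers is a plausible mechanism, not a demonstrated one, and the size of any optimism is unknown: the simulated range runs from no loss to a worst-case reversal. No sample size is affected. The plan should be changed on this point because the remedy is cheap and bears directly on Aim 4's stated purpose.

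**What to change.** 1. Add cross-validation grouped by facility or region, using the 22 hospitals and 185 clinics already in the data. All physicians and patients of a held-out group are absent from training. Assign each physician to one group by a fixed rule, such as main office, and state how patients with several physicians are placed. Compute profiles in the held-out group from that group's own history, as a new site would.
2. Report the physician-feature gain, and at least the full-model and common-data-model table entries, in held-out groups beside the year-11 result.
3. In Aim 4 (Sensitivity Analysis) and the Discussion, replace the direct-application wording with a statement that the model can be run on those systems.
4. State with the table that its outcomes assume this system's event rates and costs, and that performance in other systems is unproven until external validation.

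Cost: more computing on data already held, in a section that already foresees a computer cluster, and possibly a less favourable headline figure. Limiting step 2 to the key entries contains the workload. Items 3 and 4 are needed even if item 1 is done, since grouped testing speaks only to transfer within one system.
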